### Sample size

2.8

Considering the phase of this study (2a) to evaluate short-term safety of a drug, we have not calculated the sample size based on the previous studies. The sample size is 72 in total and 24 for each group. Assuming a dropout of about 20% and sufficient statistical power of 80% at a significant level of 0.05 in 2 tailed test, about 57 patients may be expected to complete the trials finally.

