## Discussion

3

Arthritis is the most common inflammatory disease in elderly individuals. The symptoms are characterized by inflammation, pain, and stiffness mainly in the musculoskeletal system.^[1]^

Many medications for osteoarthritis have the potential for side effects.^[2–4]^ Therefore, demands for the development of safer medication have been increased. Our previous study showed that GHJTY, a 18 herbal complex, was effective on rheumatoid arthritis by inhibiting the production of pro-inflammatory mediators and proliferation of synoviocytes.^[5]^ Other previous studies^[6]^ identified that the 5 medicinal herbs had the greatest potential, named ChondroT, from GHJTY to improve the efficacy and convenience of pharmaceutical prescription using bioinformatic method and confirmed that ChondroT had a chondroprotective effect and demonstrated multitarget mechanisms related to inflammation and arthritis which suggest ChondroT's therapeutic potential for the treatment of arthritis.^[7]^

The phase of this study is trial 2a to evaluate short-term safety of the drug. It will be a study with restrictive inclusion, exclusion criteria, and a well-controlled intervention, and will be the first randomized controlled trial to evaluate the efficacy and safety of ChondroT formula in osteoarthritis patients. However, this protocol may have limitations of the small sample size which may lead to bias. The trial according to this protocol may provide a new intervention in the treatment of osteoarthritis.

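### Section 2.8 asserts 80% power without tying it to an endpoint, comparison, difference or SD, and 24 patients per arm do not give 80% for a moderate dose-versus-placebo effect

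*Protocol article*

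**What the plan says.** Section 2.8 (Sample size) makes three statements in sequence.

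- Because the trial is phase 2a and concerned with short-term safety, "we have not calculated the sample size based on the previous studies".
- The size is then set at 72 patients, split evenly into three arms of 24.
- The closing sentence opens with "Assuming a dropout of about 20% and sufficient statistical power of 80% at a significant level of 0.05 in 2 tailed test" and concludes from this only that some 57 of the 72 should finish.

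Other sections bear on how the 80% will be read. Section 2.6 makes pain VAS after 8 weeks of treatment the primary outcome. Section 2.7 names efficacy in osteoarthritis as the primary goal. It plans a repeated-measures model with treatment at three levels and with baseline, sex and age as covariates, on a full analysis set of everyone with at least one efficacy record. The Discussion (section 3) concedes that "this protocol may have limitations of the small sample size which may lead to bias".

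**The concern.** Power is a result of the sample size, the true difference, the SD and the test. It can be a target from which a size is derived, or a property worked out for a size already chosen. Section 2.8 does neither: the size is already set, and 80% is then listed beside the dropout rate as an assumption. The only conclusion drawn, the number of completers, uses neither the power nor the alpha.

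So the 80% contributes nothing to the sentence except the assurance that the trial is adequately powered. As efficacy is the stated primary goal, a reader will attach that assurance to the pain comparison. If the comparison came out non-significant, the 80% could lend it more weight as evidence against an effect than the data would carry. Planners of a later trial could also be misled about what 24 per arm can detect.

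**Working it through.** **Inputs from the article.** 72 randomised, 24 per arm, dropout about 20%, about 57 completers, two-sided alpha 0.05, claimed power 80% (section 2.8); 1:1:1 allocation (section 2.5); baseline-adjusted model on the full analysis set (section 2.7).

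**Assumptions, not in the article.** The comparison is one dose against placebo. The correlation r between baseline and week-8 VAS is 0.5 or 0.7. The SD is 15, 20 or 25 mm, used only to convert to millimetres.

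**Step 1: the article's own figures.** 72 x 0.8 = 57.6. By arm, 24 x 0.8 = 19.2, so 19 per arm and 3 x 19 = 57. The completer count reproduces from dropout alone. The 80% cannot be reproduced, because no difference or SD is given, so the check has to run backwards.

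**Step 2: detectable difference, unadjusted.** The normal approximation is d = (1.960 + 0.842) x sqrt(2/n).

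- n = 19: 2.802 x 0.3244 = 0.91. The exact noncentral t gives 0.934.
- n = 24: 2.802 x 0.2887 = 0.81. The exact value is 0.826.
- With alpha split over the two doses (0.025 each), the exact values are 1.037 (n = 19) and 0.915 (n = 24).

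**Step 3: baseline adjustment.** As a simple approximation, multiply by sqrt(1 - r²), which is 0.866 at r = 0.5 and 0.714 at r = 0.7.

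| Difference for 80% power, alpha 0.05 (SD units) | n = 19 | n = 24 |
|---|---|---|
| Unadjusted | 0.93 | 0.83 |
| r = 0.5 | 0.934 x 0.866 = 0.81 | 0.826 x 0.866 = 0.72 |
| r = 0.7 | 0.934 x 0.714 = 0.67 | 0.826 x 0.714 = 0.59 |

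**Step 4: power at a moderate difference (0.5 SD).** Adjustment raises the effective d to 0.5/0.866 = 0.577 or 0.5/0.714 = 0.700. Exact noncentral t:

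| Power at 0.5 SD | n = 19 | n = 24 |
|---|---|---|
| Unadjusted | 32% | 40% |
| r = 0.5 | 41% | 50% |
| r = 0.7 | 56% | 66% |

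**Step 5: scale in millimetres, unadjusted.** For SD 15, 20 and 25 mm, 80% power needs 14.0, 18.7 and 23.4 mm with 19 per arm, or 12.4, 16.5 and 20.7 mm with 24 per arm.

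**Step 6: precision.** The unadjusted 95% CI half-width is t x sqrt(2/n) x SD. For n = 19 it is 2.028 x 0.3244 = 0.66 SD; for n = 24 it is 2.013 x 0.2887 = 0.58 SD. At an assumed SD of 20 mm these are about 13 mm and 12 mm.

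**The case against.** Several points on the other side are sound and limit what may be said.

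- **Not a strict contradiction.** A reader might infer that no calculation of any kind was done. The article says only that the size was not calculated from previous studies. A size can rest on an assumed effect instead, so the two statements can stand together. What remains is that no basis for the 80% is given here.
- **This is a condensed article.** Section 2.2 refers to a full protocol, version 4.51, which is not shown and may hold a difference and an SD. Their absence alone would be no finding. The fault is a positive claim whose place in the text makes it an assumption rather than a result.
- **The planned analysis beats an unadjusted test on completers.** A reader might infer that true power is about a third, or that only a very large effect is detectable. That holds for the unadjusted comparison of 19 per arm at about 0.5 SD, not across the model in section 2.7. The full analysis set can keep up to 24 per arm, and baseline adjustment helps, so a range is the honest statement.
- **Pooling the doses would help further.** Both doses together against placebo need, by the normal approximation and unadjusted, 0.79 SD with 38 versus 19, or 0.70 SD with 48 versus 24. With no dropout and r = 0.7, the latter falls to 0.70 x 0.714 = 0.50 SD. But section 2.7 keeps treatment at three levels for efficacy and states no pooled contrast, so this most favourable case cannot be taken as the basis of the 80%.
- **Modest aims are acknowledged.** The size is tied to a phase 2a purpose, and the Discussion admits the small sample. Nothing in the article says that a null result will be read as no effect. These points soften the harm but do not correct the figure, since section 2.7 makes efficacy the primary goal.

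**Conclusion.** The point holds as an unsupported power statement. The dropout arithmetic is right, and forgoing a formal calculation in phase 2a is not an error. The 80% is linked to no endpoint, comparison, difference or SD.

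For one dose against placebo at two-sided 0.05, it is true only for differences of about 0.59 to 0.93 SD or more. Where in that range depends on whether 19 or 24 per arm contribute and on an assumed baseline correlation between 0 and 0.7. Splitting alpha over two doses moves the unadjusted figures to about 0.92 to 1.04 SD. At 0.5 SD, power lies between about 32% and 66%, so 80% is not delivered for a moderate effect in that comparison. The correlations and SDs are assumptions; the unadjusted standardised figures need neither. Severity is should-fix, because the stated property is wrong or unsupported but no analysis, endpoint or enrolment figure depends on it.

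**What to change.** Delete the 80% power statement from section 2.8 and describe 72 patients (24 per arm) as a pragmatic phase 2a size. Keep the dropout sentence, which stands on its own. Alternatively, keep the 80% and state the endpoint, comparison, difference, SD and baseline correlation for which it holds.

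In either case, give what the size delivers for one dose against placebo on 8-week pain VAS:

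- a difference detectable with 80% power of about 0.6 to 0.93 SD at two-sided 0.05, with the numbers per arm and correlations behind each end;
- an unadjusted 95% CI half-width of about 0.58 SD with 24 per arm or 0.66 SD with 19.

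The cost is a change of text. The reported figure becomes less favourable; enrolment, design and analysis stay as they are.

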## Discussion

3

Arthritis is the most common inflammatory disease in elderly individuals. The symptoms are characterized by inflammation, pain, and stiffness mainly in the musculoskeletal system.^[1]^

Many medications for osteoarthritis have the potential for side effects.^[2–4]^ Therefore, demands for the development of safer medication have been increased. Our previous study showed that GHJTY, a 18 herbal complex, was effective on rheumatoid arthritis by inhibiting the production of pro-inflammatory mediators and proliferation of synoviocytes.^[5]^ Other previous studies^[6]^ identified that the 5 medicinal herbs had the greatest potential, named ChondroT, from GHJTY to improve the efficacy and convenience of pharmaceutical prescription using bioinformatic method and confirmed that ChondroT had a chondroprotective effect and demonstrated multitarget mechanisms related to inflammation and arthritis which suggest ChondroT's therapeutic potential for the treatment of arthritis.^[7]^

The phase of this study is trial 2a to evaluate short-term safety of the drug. It will be a study with restrictive inclusion, exclusion criteria, and a well-controlled intervention, and will be the first randomized controlled trial to evaluate the efficacy and safety of ChondroT formula in osteoarthritis patients. However, this protocol may have limitations of the small sample size which may lead to bias. The trial according to this protocol may provide a new intervention in the treatment of osteoarthritis.
